### Sample size

We propose to enroll 216 participants, 144 in the Tai Chi group and 72 in the aerobic exercise group. Power analyses are based on hypothesized changes in FIQR total scores. We used the outcomes of two previous randomized trials to formulate expected effects. Both studies used education controls. The first study by Rooks and colleagues [73] compared the effects of a 16-week aerobic and flexibility exercise program with an education group among 101 participants with fibromyalgia. They found that the aerobic and flexibility exercise group had a 7.9-point mean improvement in the Fibromyalgia Impact Questionnaire (FIQ), yielding an effect size of 0.62. The second study, our pilot trial of 66 participants with fibromyalgia, compared 12-weeks of Tai Chi with a wellness education control [40]. We found an 18.4-point mean improvement in the FIQ score in the Tai Chi group, yielding an effect size of 1.04. We hypothesize that patients receiving Tai Chi will improve more than those receiving aerobic exercise. Using a two-sided hypothesis test at a 0.05 significance level with an allocation ratio of 2:1, a total sample size of 216 (144 in the Tai Chi group, 72 in the aerobic exercise group) would give about 80% power to detect a conservative effect size of 0.4.

We also seek to elucidate how four different schedules of dose and frequency might modify the impact of Tai Chi. With 36 individuals per group, we would have 80% power to detect an effect size of 0.67 between two of these groups with a two-sided 0.05 level test. We will also gain power from the additional individuals tested in the other groups as well as from the blocking by instructor.

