### Data analysis

The primary outcome (change in FIQR between baseline and 24 weeks) will be compared between the five treatment groups using intention-to-treat with a two-sided significance level set at 5%. Participants who withdraw will be treated as having no change from baseline at all times after dropping out. The primary analysis will be a mixed model analysis of variance adjusting for the random blocking factor of instructor. If any characteristics differ substantially at baseline, we will adjust for them in a mixed-model regression analysis. To protect against multiple comparisons, we will only evaluate between-group differences if the overall effect of treatment is significant. If so, we will examine the following contrasts: 1) Tai Chi (four groups) versus aerobic exercise; 2) Tai Chi (12 weeks) versus Tai Chi (24 weeks); 3) Tai Chi once per week versus Tai Chi twice per week; and 4) interaction of number of treatments per week and length of treatment. We will also examine whether treatment effects differ by instructor.

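### The stated 80% power is for a direct Tai Chi versus aerobic exercise test, but the plan allows that contrast only after a significant five-group test, which leaves about 56% if the Tai Chi arms are equal

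*Protocol article*

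**What the plan says.** The Sample size section sets the numbers: "We propose to enroll 216 participants, 144 in the Tai Chi group and 72 in the aerobic exercise group". It then states the test and its power: "Using a two-sided hypothesis test at a 0.05 significance level with an allocation ratio of 2:1", this total "would give about 80% power to detect a conservative effect size of 0.4". For the dose question it adds: "With 36 individuals per group, we would have 80% power to detect an effect size of 0.67 between two of these groups".

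In the Data analysis section, change in FIQR from baseline to 24 weeks "will be compared between the five treatment groups using intention-to-treat with a two-sided significance level set at 5" per cent, in a mixed model with instructor as a random blocking factor. The rule that follows is: "To protect against multiple comparisons, we will only evaluate between-group differences if the overall effect of treatment is significant". Four contrasts are then listed: pooled Tai Chi versus aerobic exercise, 12 versus 24 weeks, once versus twice weekly, and the interaction of the last two. No further adjustment is stated for these four. The secondary outcomes follow the same template. The adjusted significance level mentioned in the next paragraph concerns only the moderator tests.

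**The concern.** The sample size rests on a comparison with one degree of freedom. The analysis makes that comparison conditional on a test with four. If Tai Chi helps by about the same amount in all four arms, the whole signal lies in one of the four dimensions that the overall test covers. That test is then clearly less powerful than the direct comparison. When it is not significant, the plan does not allow the trial's first hypothesis to be evaluated at all, even if the direct comparison would have succeeded. The stated power is therefore not the power of the planned analysis.

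The second matter is what the gate achieves. It is offered as protection against multiple comparisons. Once Tai Chi truly differs from aerobic exercise, the gate tends to be open, and the three dose contrasts are then each tested at 5% with no joint adjustment stated.

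**Working it through.** **Inputs.** From Sample size: 144 versus 72, four Tai Chi arms of 36, effect size d = 0.4, two-sided 0.05. From Data analysis: five groups, an overall test at 5%, then four contrasts. Residual degrees of freedom for five groups: 216 − 5 = 211.

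**1. The plan's own figures.**
- Noncentrality of the two-group test: 0.4 / √(1/72 + 1/144) = 0.4 / 0.1443 = 2.771.
- Power is 79.1% by the normal approximation and 78.8% by the noncentral t with 214 df. Both agree with about 80%.
- For 36 per group at 0.67: 0.67 / √(2/36) = 2.843, power 80.0% (noncentral t, 70 df). This also agrees.

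So the stated 80% belongs to the direct, ungated test.

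**2. The gate at the same inputs, Tai Chi arms equal.**
- λ = 0.4² / (1/72 + 1/144) = 0.16 × 48 = 7.68.
- The noncentral F with (4, 211) df and λ = 7.68 gives power of 57.4%.
- Simulation (arms of 72, 36, 36, 36, 36 and pooled error on 211 df) puts the chance that the overall test and contrast 1 are both significant at about 56%.
- Loss due to the gate: 78.8 − 56 ≈ 23 percentage points.
- For 80% power in the overall test, the effect would have to be about 0.50, or the total about 340 at effect 0.4.

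**3. Tai Chi arms unequal, mean effect still 0.4.** Let duration and frequency each make a difference of *a* SD, without interaction. The arm effects are then 0.4 + a, 0.4, 0.4 and 0.4 − a, and λ = 7.68 + 36 × 2a² = 7.68 + 72a².

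| a (SD) | λ | Gate and contrast 1 both significant |
|---|---|---|
| 0 | 7.68 | 56% |
| 0.1 | 8.40 | 59% |
| 0.2 | 10.56 | 67% |
| 0.3 | 14.16 | 74% |
| 0.4 | 19.20 | 78% |

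Another pattern, with two arms above 0.4 and two below it by 0.1, 0.2 or 0.3 SD, gives 62%, 73% and 78%. No pattern can exceed the ungated 78.8%, because a gate can only remove rejections.

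**4. Error across the contrasts.**
- All five groups equal: the chance of any false claim is 4.9% with the gate. Without it the chance is 18.5% (1 − 0.95⁴ = 18.5%).
- Only Tai Chi versus aerobic exercise differs: the chance of at least one false claim among the three dose contrasts is 12.3% at d = 0.4, 14.1% at 0.6 and 14.2% at 0.8. The limit is 1 − 0.95³ = 14.3%.
- Each dose contrast taken singly stays at or below 5% (4.4% at d = 0.4).

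**The case against.** **The 56% is one scenario.** It needs equal means in the four Tai Chi arms, whereas the article's second and third hypotheses expect more frequent and longer supervision to do better. This stands, and it is why a range is given. Equal arms remain the natural reading of a sample size built on a single effect size of 0.4, and modest dose differences still leave a material loss.

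**Lost trials.** A reader might infer that the gate costs the main hypothesis over 40% of trials, since it stays shut in 100 − 57.4 = 42.6% of them. That overstates the harm. The direct test itself misses in 100 − 78.8 = 21.2%, so the gate accounts for about 23 points at most.

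**The model is simpler than the planned one.** The calculation is a fixed-effects analysis. The plan has a random instructor factor and expects some gain from blocking, and withdrawals count as no change. The article gives no instructor variance and no dropout rate, so neither can be included. The comparison of gated with ungated power uses the same simplification on both sides.

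**Contrast 1 is not labelled primary.** That is true. But it is the first hypothesis, the first contrast and the basis of the sample size. If the five-group test is meant to be primary, the article states no power for it, and at the stated inputs it is about 57%.

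**Multiplicity.** A reader might infer that the gate gives no protection, or that the dose contrasts must be Holm-adjusted and placed behind contrast 1. The document does not support either. The gate works when all groups are equal, strong familywise control is not claimed, and the duration and frequency contrasts are separately stated hypotheses. The hierarchy would also be costly for a declared aim. With dose differences of 0.4 SD and no pooled effect, power per dose contrast would fall from about 60% to about 3%.

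**Conclusion.** The Sample size and Data analysis sections do not agree. The first gives about 80% power for a test that the second permits only conditionally. At the design effect with equal Tai Chi arms, the planned procedure delivers about 56%. With duration and frequency differences of 0.1 to 0.4 SD it delivers about 59% to 78%. These figures rest on normal outcomes with a common variance and full arms of the planned size, and they leave out instructor variance and dropout. An unqualified 56% would say more than the document supports.

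The error-rate point is secondary. The gate limits error across the contrasts only when all five groups are equal. If Tai Chi truly differs from aerobic exercise, the chance of some false dose claim is about 12% to 14%. That is a reason not to describe the gate as full protection, but it does not make an adjustment obligatory.

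**What to change.** - Name contrast 1, pooled Tai Chi versus aerobic exercise, as the single primary test at two-sided 5%, without the overall gate. This restores the stated power (78.8% at 0.4).
- The 4-df test can remain as the gate for contrasts 2 to 4. They need not depend on contrast 1.
- If the gate on contrast 1 is kept, restate the power as about 56% with equal Tai Chi arms, and about 56% to 78% depending on dose differences.
- Say plainly that the overall test limits error across the contrasts it guards only when all groups are equal. Whether to adjust contrasts 2 to 4, for example by Holm, is the sponsor's choice and should be stated either way.

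The cost is wording only, with no extra participants or data, but the change must be made and dated before any unblinded analysis. There is one statistical price. With contrast 1 outside the gate, the chance of any false claim when all five groups are equal is no longer held at 5%. It is bounded by 5% for contrast 1 plus 5% for the gate, that is 10%. The protocol should acknowledge this, with contrast 1 alone carrying the primary claim.

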**Discussion:**

This study is the first comparative effectiveness randomized trial of Tai Chi versus aerobic exercise in a large fibromyalgia population with long-term follow up. We present here a robust and well-designed trial to determine the optimal frequency and duration of a supervised Tai Chi intervention with regard to short- and long-term effectiveness. The trial also explores multiple outcomes to elucidate the potential mechanisms of Tai Chi and aerobic exercise and the generalizability of these interventions across instructors. Results of this study are expected to have important public health implications for patients with a major disabling disease that incurs substantial health burdens and economic costs.

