### Randomization

Randomization occurs after the baseline evaluation. The study statistician ([name]) randomizes assignments using a sequence randomly generated in the R statistical package [41]. These assignments are then sent to a study staff member other than the study coordinator or principal investigator, who puts them into sealed, opaque envelopes with date and signature labels placed over the seals of the envelopes. The study coordinator then contacts eligible participants by phone, and confirms that each one still wishes to participate in the study and is able to make the time commitment to either intervention group. Upon confirmation, the study coordinator opens the consecutive randomization envelope and informs the individuals of their group assignments. The study coordinator also informs the participants of the schedule for their training sessions (including date and time). Randomization envelopes are not opened unless a participant meets eligibility criteria, completes the informed consent, and undergoes a baseline assessment.

The study is conducted in six different cycles. Each cycle consists of an aerobic exercise intervention group and two of the four Tai Chi intervention groups. The Tai Chi intervention groups are rotated through the six cycles so that each one (12 or 24 weeks of supervised Tai Chi, once or twice per week) occurs three times over the course of the study. We use a factorial arrangement to ensure that each of the three Tai Chi instructors conducts each of the four treatments (Tai Chi once or twice per week for each of 12 and 24 weeks) once during the trial. This arrangement is subject to the constraints that two sessions are given in each of the six cycles, that each instructor teaches twice in each of the first three and last three cycles, that no instructor teaches more than once in any single cycle and that each treatment is given at least once and no more than twice in the first three sessions and in the last three sessions. Each instructor is therefore idle for two of the six sessions. The design for each of the four treatments (A, B, C and D) is listed in Table 3. The instructors are randomly assigned to be I, II or III, and each of the four treatments is randomly assigned to be A, B, C or D. Each resulting group consists of 12 patients, for a total of 36 patients participating in each cycle and 216 over the course of the six cycles comprising the study.

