## Discussion

In this project, we are conducting the first randomized comparative effectiveness trial of Tai Chi versus aerobic exercise in a large fibromyalgia population with long-term follow-up. We present here the plan for a robust and well-designed trial to determine the optimal frequency and duration of a supervised Tai Chi intervention in relation to short- and long-term effectiveness.

Emerging evidence suggests that Tai Chi mind-body exercise has potential therapeutic benefits for fibromyalgia.

Specifically, prior studies have shown that 12 weeks (once to twice per week) of Tai Chi or aerobic exercise is the minimum intervention and practical length needed to achieve effective benefits, especially among beginners [13,14,22,23,26,40]. Further, patients with fibromyalgia have also benefited from 24 weeks of Tai Chi but it is unclear if this longer duration offers better results than a 12-week program.

Hence, the optimum dose and length (frequency or duration) of supervised Tai Chi practice as a treatment for fibromyalgia have not yet been conclusively determined. Optimal clinical implementation remains unknown. In this study, we are comparing 12 weeks of supervised Tai Chi versus 24 weeks of supervised Tai Chi, at two frequencies (one or two times per week), to determine the optimal dose and length of supervised Tai Chi needed for clinical application, compared to 24 weeks of supervised aerobic exercise. We propose to determine the effectiveness of Tai Chi exercise compared to aerobic exercise as well as its clinical utility in a larger scale study over a longer period of time. In addition, testing durability of the supervised exercise up to 52 weeks based on prior data will provide much needed treatment information.

Moreover, investigating multiple secondary outcomes will elucidate the potential mechanisms of mind-body effects. To address one of the unanswered questions from our previous studies about whether the observed benefit of Tai Chi was localized to the instruction of a single instructor or whether the observed benefit could be generalized to others. Systematic differences across instructors would imply that the amount of treatment benefit might depend on the skill level of the individual instructor; lack of differences would imply that the benefit might apply more generally.

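### Each instructor-by-schedule cell is one class, so that interaction cannot be told apart from class differences, and the stated model makes any instructor test too liberal if classes differ

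*Protocol article*

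**What the plan says.** Under Randomization, the protocol article arranges that "each of the three Tai Chi instructors conducts each of the four treatments" once in the trial, in groups of 12. Table 3 shows the result: 12 instructor-by-schedule cells, each filled by one class in one cycle. Each of the six cycles also contains one aerobic exercise class.

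Under Data analysis, the primary model is a mixed-model analysis of variance with instructor as a random blocking factor and a "two-sided significance level set at 5" per cent. No class or cycle term is named. After the four planned contrasts the section adds: "We will also examine whether treatment effects differ by instructor". The secondary analyses follow the same template, check interactions that include treatment and instructor, and pool results across instructors if the instructor effect is not significant.

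The Abstract names "the generalizability of these interventions across instructors" among the things the trial explores. The main Discussion fixes the reading in advance: "Systematic differences across instructors would imply that the amount of treatment benefit might depend on the skill level of the individual instructor". It reads a lack of differences as a sign that the benefit applies more generally.

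**The concern.** A participant-level test of instructor differences treats the 12 people in a class as independent given instructor and schedule. They share a room, a group, a start date and a season. If one class does well or badly for any of those reasons, the stated model has nowhere to put the difference except instructor or instructor-by-schedule, and the Discussion would read it as instructor skill.

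At stake is a stated aim of the trial: whether the Tai Chi benefit carries over from one instructor to another. The instructor test also decides whether results are pooled, so a wrong error rate affects how the secondary results are presented.

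**Working it through.** **Inputs from the protocol article.** Three instructors, four schedules, one class per cell, 12 participants per class; six cycles, each with two Tai Chi classes and one aerobic class, so 18 classes in all (Randomization, Table 3). Instructor is the only grouping factor (Data analysis). The class ICC is not given. It is assumed here, over the range 0 to 0.10.

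**The plan's own figures.** The article states no power or error rate for the instructor question. Its sample-size figures do reproduce.

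- "We propose to enroll 216 participants, 144 in the Tai Chi group and 72 in the aerobic exercise group"; this "would give about 80% power to detect a conservative effect size of 0.4". A two-sided 5% comparison of 144 with 72 at effect size 0.4 gives 79.1% (78.8% using the t distribution).
- "With 36 individuals per group, we would have 80% power to detect an effect size of 0.67 between two of these groups". This gives 81.1% (80.1% using the t distribution).

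Both calculations treat participants as independent.

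**Step 1: degrees of freedom among the Tai Chi classes.** Twelve classes give 11 degrees of freedom: 3 for schedule, 2 for instructor and 3 × 2 = 6 for their interaction. 11 − 3 − 2 − 6 = 0, so nothing is left for class-to-class variation. Class and instructor-by-schedule are the same 12 cells.

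**Step 2: cycle.** Ranks of the design matrix built from Table 3:

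| Classes used | Treatment + instructor + interaction | The same + cycle |
|---|---|---|
| 12 Tai Chi | 12 | 12 |
| All 18 | 13 | 18 |

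With Tai Chi classes alone, cycle is absorbed by the interaction. With the aerobic classes included, the rank rises by 5, so additive cycle effects can be estimated. That model is saturated (18 parameters for 18 classes) and still leaves nothing for class.

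**Step 3: true size of a nominal 5% participant-level test that omits class.** With no true effect, the ratio of expected mean squares is

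inflation = 1 + 12 × ICC / (1 − ICC).

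True size = P(F > critical value / inflation), with 12 × (12 − 1) = 132 residual degrees of freedom. The 5% critical values are 2.168 for F(6, 132), the interaction, and 3.065 for F(2, 132), the instructor main effect.

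| Assumed class ICC | Inflation | Interaction | Instructor main effect |
|---|---|---|---|
| 0 | 1.00 | 5.0% | 5.0% |
| 0.01 | 1.12 | 8.0% | 6.9% |
| 0.02 | 1.24 | 11.6% | 8.9% |
| 0.05 | 1.63 | 24.9% | 15.7% |
| 0.10 | 2.33 | 47.6% | 27.2% |

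Example at ICC 0.05: inflation = 1 + 12 × 0.05 / 0.95 = 1.63; 2.168 / 1.63 = 1.33; P(F(6, 132) > 1.33) = 24.9%.

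**Step 4: simulation check.** 4,000 runs with 18 classes of 12 and fixed-effect analysis of variance:

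- Class ICC 0.05, no cycle variance: interaction test size about 25% without cycle terms and 24% with them.
- Cycle variance 5% of the total, no class variance: about 28% without cycle terms and 6% with them.

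Cycle terms therefore remove the cycle part of the problem and leave the class part.

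**Step 5: what can be tested.** Each instructor teaches four classes, so the main effect is replicated. With all 18 classes, treatment + cycle has rank 10 and adding instructor gives 12. That leaves 18 − 12 = 6 class-level degrees of freedom, hence a test on 2 and 6. Using only the 12 Tai Chi class means also gives 2 and 6, but cycle variance then enters the instructor mean square with coefficient 0.5 and the error mean square with 1.17. That test is conservative if cycles differ.

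**The case against.** Four points can be made for the plan.

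- **The sentence is loose, and the Discussion asks about the amount of benefit.** That points to the instructor main effect, which is replicated over four classes. This stands, and it makes the problem smaller (16% rather than 25% at ICC 0.05). It does not remove it, because the main-effect test is also too liberal when class is omitted.
- **Cycle is handled by design.** The article runs the arms concurrently because of season. This stands as far as the design goes: a reader might infer that cycle or season can never be separated from instructor, and the aerobic classes show otherwise. The stated model does not use them for this.
- **No ICC is given, so nothing shows that the test will often be falsely positive.** This stands. A reader might infer frequent false positives, but the excess is nil at ICC 0 and mild at 0.01. The size is conditional on the assumed ICC; the aliasing of class with the interaction is not.
- **The error term belongs in the statistical analysis plan.** This stands only in part. The article itself states the grouping factor, the question, the pooling rule and the interpretation, and no later document can supply a second class per cell.

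A reader might also infer that the authors intend to say the best schedule depends on who teaches. The article makes no such claim. The wording in the Abstract about both interventions is minor, since the Discussion confines the question to Tai Chi.

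**Conclusion.** The concern holds in a limited form. Instructor-by-schedule is wholly confounded with class by the design and, in the stated model, also mixed with cycle. If classes differ at all, participant-level instructor tests exceed their nominal 5%: about 8% to 48% for the interaction and 7% to 27% for the main effect over class ICC 0.01 to 0.10. These sizes rest on an assumed ICC, equal classes of 12 and a fixed-effect analysis of variance; at ICC 0 there is no inflation. The instructor main effect can be tested validly, though weakly. This point concerns the instructor question and the pooling rule that depends on it; it makes no claim about the primary contrasts.

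**What to change.** In the Data analysis section:

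1. For the instructor question, use all 18 classes and add cycle and class terms.
2. Test the instructor main effect, which is the question in the Discussion, against class-level variation on 2 and 6 degrees of freedom.
3. Report the 12 instructor-by-schedule class means descriptively, with no significance test and no claim that schedule effects depend on the instructor.
4. Limit the generalisability statement to Tai Chi instructors averaged over the four schedules.
5. Do not let a non-significant instructor test by itself stand as evidence of no instructor differences. This applies to the pooling rule and to the Discussion.

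The cost is analysis work and wording only; no new data are needed. The price is power: the 5% critical value rises from 3.06 on 2 and 132 degrees of freedom to 5.14 on 2 and 6. Removing cycle effects also relies on a single aerobic class per cycle.

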### Tai Chi intervention

The participants randomized to Tai Chi will practice at Tufts Medical Center. A detailed description of a standardized Tai Chi protocol was prepared and tested in our previous trials [23,25,26,32,39]. The three Tai Chi instructors each have extensive experience (>20 years) conducting Tai Chi mind-body programs and follow a Tai Chi protocol specifically designed for individuals with chronic pain. In addition, all three instructors completed the required research and human subject protection training prior to initiation of the intervention classes.

To ensure that instructors are prepared to teach a robust, standardized Yang-style Tai Chi treatment program for patients with fibromyalgia, we conduct a training session with the three Tai Chi instructors to thoroughly review concepts of fibromyalgia and a standardized teaching protocol at the beginning of the study and are doing reviews as needed throughout the course of the study. All sessions are monitored by regularly reviewing video recordings and providing feedback throughout the study to ensure proper instruction.

Each Tai Chi session lasts 60 minutes and continues once or twice a week for 12 weeks or 24 weeks. Participants are also provided with printed materials on the Tai Chi Mind-Body program, including Tai Chi principles, practicing techniques, and safety precautions for participants with fibromyalgia. In the first session, the Tai Chi instructor explains exercise theory and Tai Chi procedures. For the remaining sessions, the procedures include the following components: (1) warm-up and a review of Tai Chi principles and techniques; (2) Tai Chi movement; (3) breathing techniques; and (4) various relaxation methods. All program components are derived from classical Yang style Tai Chi 108 postures [42]. Due to time limitations [22] we condensed the 108 postures of Classical Yang style Tai Chi to 10 forms that could be learned by participants with a chronic pain condition within 12 or 24 weeks. The 10 forms were selected because: (1) they are easily comprehensible; (2) clearly represent progressive degrees of stress to postural stability, with weight bearing moving from bilateral to unilateral supports; and (3) seem to emphasize increasing magnitude of trunk and arm rotation with diminishing base of support and, as such, will potentially improve physical function without excessively stressing the joints. An outline of the Tai Chi exercise program is shown in Additional file 2.

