Secondary analyses will examine change in FIQR from baseline to 12 and 52 weeks as well as secondary outcomes for change at 12, 24, and 52 weeks. Continuous outcomes will be compared by linear regression, and discrete outcomes by logistic regression. All analyses will follow the template for the primary outcome in the previous paragraph, using mixed models with adjustment for instructor examining treatment duration and frequency. If the instructor effect is not significant, we will present results summarized across instructors. All regression models will be assessed by regression diagnostics for adherence to model assumptions. To explore potential psychological and psychosocial mediators (for example, depression, self-efficacy, social support) that may be useful in future research, we will examine treatment interactions with a list of pre-defined moderators. To control for multiple testing, we will perform these tests at a conservative significance level adjusted for the number of moderators tested. In addition, we will also perform longitudinal analyses in which measurements at baseline, 12, 24, and 52 weeks are jointly analyzed using appropriate mixed models including time as a categorical fixed factor with random intercepts and first-order autocorrelation of the errors. Similar mixed models will be used to examine the weekly FIQR measurements taken in the intervention period. We will also check for potential confounding and interaction between time, treatment, instructor and other significant covariates. In addition to intent-to-treat analyses in which dropouts are treated as having no effect, we will also perform secondary analyses using multiple imputation and checks of the mechanism by which participants drop out to determine whether ignorable or nonignorable missing data methods are required [74,75]. If nonignorable methods are needed, we will explore both selection and pattern-mixture types [74,75].

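### The week-12 secondary analyses keep the five-group gated template, although two of its four degrees of freedom have no scheduled treatment difference behind them at that visit

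*Protocol article*

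**What the plan says.** For the primary outcome, the Data analysis section of the protocol article says that change in FIQR at 24 weeks "will be compared between the five treatment groups" at a two-sided 5% level. It adds a gate: "we will only evaluate between-group differences if the overall effect of treatment is significant". Four contrasts follow if the gate opens. One is Tai Chi versus aerobic exercise and one is once versus twice weekly. The other two involve duration: "2) Tai Chi (12 weeks) versus Tai Chi (24 weeks"), and "4) interaction of number of treatments per week and length of treatment".

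The next paragraph of that section begins "Secondary analyses will examine change in FIQR from baseline to 12 and 52 weeks" and adds the other outcomes at 12, 24 and 52 weeks. It then says "All analyses will follow the template for the primary outcome in the previous paragraph", and names both duration and frequency as factors to be examined. It makes no exception for week 12.

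On the treatment itself, the Tai Chi intervention section says "Each Tai Chi session lasts 60 minutes and continues once or twice a week for 12 weeks or 24 weeks". It gives one list of session components and one home-practice instruction for all Tai Chi participants. The Randomization section has each of the three instructors teach each of the four Tai Chi schedules once.

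**The concern.** Hypothesis 3 in the Background is that 24 weeks of supervised Tai Chi does better than 12 weeks. At the week-12 visit the same-frequency arms have not yet diverged in scheduled dose: one is finishing its classes and the other is halfway through. The duration contrast and the frequency-by-duration interaction thus have no dose difference to detect, yet both are part of the overall test that must be significant before any other week-12 comparison is made.

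Two things are at stake. The gate is weaker than it need be for the two questions that week 12 can answer: Tai Chi versus aerobic exercise, and once versus twice weekly. And when the gate does open, two contrasts that cannot inform the choice between 12 and 24 weeks of classes are tested and may turn out significant by chance. More than 20 rows of Table 1 are marked for week 12, so this recurs across many outcomes.

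**Working it through.** **Inputs from the article.** The Sample size section gives 216 participants, 144 Tai Chi (four arms of 36) and 72 aerobic exercise, and a design effect of 0.4 SD. The Data analysis section gives five groups, a 5% level and the gate. **Assumptions.** All 216 are analysed, errors are independent with unit SD, and there is no instructor variance. The 0.4 SD is borrowed from the week-24 design because no week-12 effect is given, so a range is shown.

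**1. The article's own figures.** Two-group comparison, 144 versus 72, 0.4 SD, two-sided 5%: power 0.791 (normal) or 0.788 (noncentral t), against the stated value of about 80%. For 36 versus 36 at 0.67 SD: 0.811 or 0.801, against the stated 80%. Both reproduce.

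**2. What the four degrees of freedom are.** Five groups give 4 numerator df: Tai Chi versus aerobic exercise, frequency, duration, and frequency by duration. At week 12 the last two have no scheduled treatment difference behind them.

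**3. Noncentrality.** λ = Σ nᵢ(μᵢ − μ̄)². If every Tai Chi arm differs from aerobic exercise by d, this is d² × 144 × 72 / 216 = 48d². At d = 0.4, λ = 48 × 0.16 = 7.68. If same-frequency arms share a mean, merging them leaves λ unchanged and changes only the df: (4, 211) with critical F 2.414 becomes (2, 213) with critical F 3.038.

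**4. Power of the overall test at week 12.**

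| Assumed Tai Chi effect versus aerobic exercise | λ | Five groups, 4 df | Three groups, 2 df |
|---|---|---|---|
| 0.3 SD in every arm | 4.32 | 33.7% | 43.9% |
| 0.4 SD in every arm | 7.68 | 57.4% | 69.2% |
| 0.5 SD in every arm | 12.00 | 79.2% | 87.8% |
| 0.6 SD in every arm | 17.28 | 92.7% | 96.7% |
| 0.3 SD once weekly, 0.5 SD twice weekly | 9.12 | 65.9% | 77.0% |

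For the last row the overall mean is (72 × 0.3 + 72 × 0.5 + 72 × 0)/216 = 0.267, so λ = 72 × (0.033² + 0.233² + 0.267²) = 9.12.

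At 0.4 SD in every arm, the probability of passing the gate and then finding Tai Chi versus aerobic exercise significant is 55.7% with five groups and 67.8% with three (simulation, 200,000 replicates).

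**5. Chance duration or interaction results under the plan's gate.** Simulation of the five-group test followed by the two contrasts at 5% each, with same-frequency arms equal (400,000 replicates):

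| Tai Chi effect | Gate passes | At least one of the two contrasts declared significant |
|---|---|---|
| 0 | 4.9% | 2.9% |
| 0.3 SD | 33.8% | 6.9% |
| 0.4 SD | 57.4% | 8.5% |
| 0.6 SD | 92.7% | 9.6% |

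A separate run of 200,000 gave 2.8% with no effect and 8.3% at 0.4 SD, so about 3% and 8% are fair roundings.

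**The case against.** Much of the case on the other side stands.

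- **The template is valid.** A five-group test keeps its size and its contrasts are unbiased. Pooling is a gain in efficiency, not the repair of a false statement.
- **Only secondary analyses are involved.** At weeks 24 and 52 the duration contrasts are meaningful. The Sample size section makes no power claim for week 12, and the planned longitudinal model offers another route to week-12 estimates.
- **An unseen analysis plan may set visit-specific contrasts.** That is possible, but the article does not leave the matter open: it applies the template to all analyses and names duration.

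Several stronger readings are tempting, and the article does not support them.

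- **That the arms are identical and the contrasts null by design.** Only the scheduled dose and home practice are shown to be the same. The Tai Chi intervention section says the forms could be learned in 12 or 24 weeks, and the programme outline (Additional file 2) is not shown, so different pacing cannot be excluded. Participants know their assignment, and the arms are separate classes in partly different cycles (Table 3). Even so, a difference from pacing, expectancy or class would not show the effect of 24 rather than 12 weeks of classes.
- **That the false-positive chance is 1 − 0.95² = 9.75% for every outcome.** This ignores the plan's gate. It is a ceiling, approached only when the gate nearly always opens, which is where the power loss becomes small.
- **That the plan would present a week-12 duration result as evidence on optimal duration.** It says only that duration is examined.
- **That the two extra df explain the whole gap between 79% and 57%.** They account for about 12 points. The 2-df gate still gives 69%, and the rest comes from placing a 1-df contrast behind an overall test.

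**Conclusion.** The point holds for the week-12 secondary analyses and no further. The article carries the five-group gated template, with its duration and interaction contrasts, to a visit at which same-frequency Tai Chi arms have had the same scheduled supervised dose and home practice. The cost is about 12 percentage points of overall-test power at 0.4 SD, about 10 at 0.3 SD, 9 at 0.5 SD and 4 at 0.6 SD. There is also a gated chance of about 3% to just under 10% per outcome of a duration or interaction result that reflects no difference in scheduled treatment.

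These sizes rest on 216 analysed, independent errors, equal means in same-frequency arms, and effect sizes that the article does not give for week 12. Dropout and instructor variance would change the power levels but not the argument about degrees of freedom. The primary week-24 analysis is not affected. It is a worthwhile and cheap improvement, not a threat to the trial's main conclusion.

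**What to change.** In the Data analysis section, add an exception for week 12. Use three groups (once-weekly Tai Chi, twice-weekly Tai Chi and aerobic exercise, 72 each) with a 2-df overall test. If it is significant, test Tai Chi versus aerobic exercise and once versus twice weekly. Drop the duration and interaction contrasts at that visit, and show the 12-week and 24-week arms side by side descriptively. Keep the five-group template at weeks 24 and 52.

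The longitudinal model need not be forced to a common week-12 mean for same-frequency arms. That would impose an equality which the article does not establish, and the gain described here does not depend on it.

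The change needs wording only and no new data. The price is that a week-12 difference due to anticipation or class pacing is no longer formally tested.
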